**Methods:**

In this Randomized Controlled Trial, a total of 240 first-year university students (*n* = 80 per condition) will be randomized into one of three conditions: (1) a smartphone condition, (2) a VR condition, and (3) an active control condition. We will assess proximal (i.e., future self-identification) and distal intervention outcomes (e.g., future orientation, self-defeating behaviors, goal achievement), user engagement, and examine usage data and goal content. Assessments will take place at baseline, during the intervention, immediately after the intervention, and at 3- and 6-months follow-up.

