### Participants and power calculation

We will include first-year students from a university in the Netherlands. Students with epilepsy will be excluded due to increased risk of seizures in VR. To determine sample size an a-priori power analysis was conducted with G*Power. We based our estimate of the effect size on a review of meta-analyses which showed that Cohen’s *d* effect sizes of universal interventions range from 0.23 to 0.58 [32]. Assuming a medium effect size of Cohen’s *d* = 0.40, a significance level of *p* < 0.05, three conditions, and one covariate, a sample size of 199 participants is estimated for a power of 80%. Based on a drop-out rate of 20%, we aim to include 240 participants, i.e., 80 participants per condition.

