### Recruitment and randomization

To recruit participants we will distribute flyers in university buildings and use communication channels of the university where the study is conducted, such as the university website and various social media channels. Additionally, we will ask student associations to distribute the advertisement of the study among their members.

Students interested in participating can schedule an appointment for the intake using an online portal. Before the intake, students are assessed for eligibility and randomly assigned to a condition on a 1:1:1 ratio using block randomization with blocks of 9, so that within a block three participants are allocated to each of the three conditions.

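### With 20% drop-out, 240 randomized leaves 192 evaluable, 7 short of the 199 the plan says it needs; the allowance appears to be 199 × 1.2 rather than 199 / 0.8

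*Protocol article*

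**What the plan says.** The section on participants and power calculation in the Protocol article reports that "an a-priori power analysis was conducted with G*Power". The inputs are given as "Assuming a medium effect size of Cohen’s *d* = 0.40", "a significance level of *p* < 0.05" and "three conditions, and one covariate". From these, "a sample size of 199 participants is estimated for a power of 80" per cent. The drop-out allowance follows directly: "Based on a drop-out rate of 20%, we aim to include 240 participants, i.e., 80 participants per condition". No inflation formula is shown. The Methods paragraph of the abstract repeats the target as "a total of 240 first-year university students", with 80 per condition.

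**The concern.** A drop-out rate is a fraction of those enrolled. To have a given number left after a 20% loss, the requirement is divided by 0.80. Multiplying it by 1.20 falls short, because the 20% is then taken from a larger base than the one it was added to. The stated target of 240 looks like the product of that second route.

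At stake is whether the published justification is true on its own terms. A reader will take it that the trial keeps 80% power if one participant in five is lost. The Discussion itself warns that drop-out tends to be relatively high in studies of new technologies and that repeated measurement adds to participant burden, so the allowance may well be needed in full.

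**Working it through.** **Inputs, all from the section on participants and power calculation:** required sample 199; target power 80%; drop-out 20%; target enrolment 240 (80 × 3); d = 0.40; alpha 0.05; three groups; one covariate.

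**Step 1: the base figure.** The article gives neither the effect-size scale used in the software nor the numerator degrees of freedom. I assumed f = d/2 = 0.20 and one numerator degree of freedom. In the fixed-effects ANCOVA model, power comes from the noncentral F distribution with noncentrality λ = f² × N and denominator df = N − groups − covariates.

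- N = 198: power 0.7996
- N = 199: λ = 0.04 × 199 = 7.96, df = 199 − 3 − 1 = 195, power 0.8016

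The smallest N reaching 80% is therefore 199, which matches the stated figure exactly.

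**Step 2: the drop-out allowance.**

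| Route | Calculation | Result |
|---|---|---|
| Divide by the retained fraction | 199 / 0.80 = 248.75 | 249 (83 per condition) |
| Add 20% to the requirement | 199 × 1.20 = 238.8 | 239, or 240 in three equal arms |

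The stated 240 agrees with the second route and is 9 below the first.

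**Step 3: what 240 delivers.**

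- Evaluable at 20% drop-out: 240 × 0.80 = 192
- Shortfall: 199 − 192 = 7
- Largest drop-out that keeps 199: 1 − 199/240 = 0.171, or 17.1%
- If each participant independently has a 20% chance of loss, the probability of ending below 199 is about 85%

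**Step 4: power at 192.** In the Step 1 model, λ = 0.04 × 192 = 7.68 and df = 188, giving power 0.787. That is 1.3 points below 80% and 1.4 points below the 80.2% at 199.

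Step 3 needs only the printed figures; only the power in Step 4 depends on the reconstruction in Step 1.

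**The case against.** The case for leaving this alone has four parts.

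- **The mechanism is inferred.** No formula is printed, so 199 × 1.2 is the likely route and not a documented one. The same applies to the model behind 78.7%. Both points stand. Neither affects the shortfall of 192 against 199.
- **The effect is trivial.** At 192, 80% power is reached at d = 0.406 instead of 0.40. The article takes 0.40 from a range of 0.23 to 0.58, over which power at 192 runs from about 35% to 98%. This is a fair reason to rate the point low. It is not a reason to leave the sentence uncorrected.
- **The planned analysis may make up the loss.** The reconstructed calculation charges the baseline covariate one degree of freedom and credits it with no explained variance. If d = 0.40 is on the unadjusted scale, a baseline–outcome correlation of 0.2 brings power at 192 to 80.3%, and 0.3 brings it to 82.4%. The article gives no correlation and does not say which scale d is on, so this is possible but is not part of the stated justification. What it does limit is the claim: the miss is against the plan's stated assumptions and need not be a miss in actual power.
- **Intention-to-treat keeps everyone, and 20% is not tied to a time point.** Including all randomized participants does not supply outcomes that were never recorded, and the Design section treats late questionnaires as missing data. The plan also adds a drop-out allowance to 199, so it counts drop-outs as lost information. It is true that the number evaluable will differ by outcome and visit.

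**Conclusion.** The concern holds. On the printed figures alone, 240 with 20% drop-out yields 192 and not 199; 249 would be needed, and 240 covers drop-out only up to 17.1%. Nothing elsewhere in the article reconciles these numbers.

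The power consequence is small: 78.7% at 192, assuming f = 0.20, one numerator degree of freedom, three groups, one covariate and no variance explained by that covariate. That 20% was added on top is an inference, though a strong one, because it lands on the stated target.

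This point accepts 199 as given. Whether a calculation with one numerator degree of freedom suits a three-arm comparison is a separate question.

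**What to change.** Correct the drop-out sentence in the section on participants and power calculation in one of two ways:

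- With 240 randomized and 20% drop-out, 192 participants are expected to be evaluable, giving power of about 79% on the stated assumptions.
- With 240 randomized, the design keeps the required 199 for drop-out up to about 17%.

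The text should also show the inflation formula, so that a reader can check the step. The 240 in the abstract can stay as the enrolment target. The cost is one sentence and a slightly less favourable power statement; enrolment, allocation and analysis are unchanged.

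If the authors would rather keep both 20% and 80%, the target becomes 249 (249 × 0.80 = 199.2). Since the section on recruitment and randomization has students "randomly assigned to a condition on a 1:1:1 ratio using block randomization with blocks of 9", whole blocks would mean 252, or 84 per condition. For a gain of just over one point of power that is optional, and the correction does not require it.

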### Recruitment and randomization

To recruit participants we will distribute flyers in university buildings and use communication channels of the university where the study is conducted, such as the university website and various social media channels. Additionally, we will ask student associations to distribute the advertisement of the study among their members.

Students interested in participating can schedule an appointment for the intake using an online portal. Before the intake, students are assessed for eligibility and randomly assigned to a condition on a 1:1:1 ratio using block randomization with blocks of 9, so that within a block three participants are allocated to each of the three conditions.

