## Method

### Design

The current study regards an iteration and extension of a prior pilot RCT [see 31] evaluating the first version of the FutureU app. In the present study, the intervention will be examined through an RCT with three conditions: (1) a smartphone condition in which the intervention is implemented via (an iteration of) the FutureU app, (2) a VR condition in which the intervention is delivered through immersive VR, and (3) an active control condition in which participants set goals but receive no further intervention. Ethical approval was obtained from the independent Ethics Board of the Institute of Education and Child Studies at Leiden University (ECPW2021-320). The trial was registered on Clinicaltrials.gov (NCT05578755) on 13 October 2022.

In all conditions, participants start with an intake session. During this session participants give active informed consent, set personal goals, and complete an online questionnaire. In both intervention conditions, an avatar will be created and aged using a machine learning-based algorithm to generate a digital version representing their 10-year older, and hence ‘future’, self (see ‘Avatar Creation’ below).

All participants complete online questionnaires at baseline (i.e., during intake), at weekly intervals during the intervention (assessing a subset of the outcome variables), immediately after the intervention (i.e., three to four weeks after the intake), and at 3- and 6-months follow-up. For the smartphone condition, assessments occur on the 7th day of each of the three week-long modules (i.e., day 7, day 14, and day 21 of the intervention). For the VR condition, assessments occur at the start of the subsequent VR session about a week later. Additionally, future self-identification and the VR experience items are (also) assessed immediately after each VR session. For the control condition, assessments occur at time points parallel to those of the smartphone condition. Questionnaires not completed in time (i.e., within 4 days for the interim measurements, within 8 days for the post measurement, within 16 days for the 3-months follow-up, and within 32 days for the 6-months follow-up) will be treated as missing data.

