### Blinding

Blinding is not possible as all individuals involved will know whether the app or VR will be used or not. However, participants are unaware of the intervention’s content and the study’s hypotheses.

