### Conditions

#### Intervention

The intervention starts with participants setting two personal goals during the intake, one goal goal they want to have achieved within a month and one that they want to have achieved in the coming year.^2^ The formulation of these goals is guided by the researcher and follows the SMART-goal model and Zimmerman’s criteria [33]. These guidelines facilitate setting specific, measurable, and challenging but attainable goals – characteristics that are most likely to foster goal attainment [34]. Additionally, each week participants independently set a new goal that functions as the next step towards achieving their month goal (participants in the VR condition receive additional guidance – see ‘VR Condition’ below).

The intervention consists of three modules aimed at (1) instilling a more vivid view of the future self, (2) stimulating future-oriented decision making, and (3) setting and achieving personal goals. Table 1 provides an overview of the three modules, their theoretical foundation, and the translation of the underlying theory into core features and interactions of (the current iteration of) the app and VR.

**Table 1 Tab1:** Description and Features of the Three Intervention Modules

Module	Theory	Core features Smartphone app	Core features VR sessions

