##### Statistical analyses

The data will be analyzed using an intention-to-treat approach which implies that all randomized participants will be included in the analyses regardless of whether they actually completed the intervention or not. The three conditions will be compared on age and gender to examine potential differences at baseline. In case of baseline differences between the conditions, we will correct for them in the analytical models.

To test the effectiveness of the intervention and investigate differences in intervention effects between the two implementation methods, we will use regression models and ANCOVAs with the baseline measure of the concerned outcome as a covariate. Mediation will be examined with regression analyses. We will analyze whether the intervention conditions are associated with changes in the mediators (e.g., vividness, valence, and relatedness) and whether these changes, in turn, are related to changes in the intervention outcomes. Moderation of intervention effects will be analyzed with interaction effects in regression models and multigroup models.

Furthermore, we will study how (fluctuations in) usage patterns and engagement levels in an app and VR change over time and relate to intervention outcomes in an exploratory fashion using regression analyses possibly complemented with additional analyses (e.g., latent profile models). We will also qualitatively examine participants’ goal content, coding aspects such as the degree of specificity, the difficulty level, and the topic. Additionally, we will explore the role of goal content within the future self-identification framework. More specifically, we will relate aspects of goal content to the future self-identification scales (i.e., vividness, valence, and relatedness) over time, and examine the potential mediating role of self-efficacy in this context. Both will be analyzed with regression analyses.

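### Students are randomized before consent, goal setting and baseline: the all-randomized rule fails for any who never attend or consent, and baseline and goals are exposed if the arm is known

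*Protocol article*

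**What the plan says.** **Allocation.** Under Recruitment and randomization, the contact described before the intake is a booking: "Students interested in participating can schedule an appointment for the intake using an online portal". Allocation follows: "Before the intake, students are assessed for eligibility and randomly assigned to a condition on a 1:1:1 ratio using block randomization with blocks of 9".

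**Intake.** The Design section says of the intake: "During this session participants give active informed consent, set personal goals, and complete an online questionnaire". It confirms the timing of T1: "All participants complete online questionnaires at baseline (i.e., during intake". Of the month and year goals, the Intervention section says: "The formulation of these goals is guided by the researcher". The Control condition section applies the same intake procedure to controls. The Avatar creation section puts the smartphone arm's selfie at the intake and the VR avatar at the first VR session.

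**Blinding.** "Blinding is not possible as all individuals involved will know whether the app or VR will be used or not". The section adds that participants do not know what the intervention contains or what is hypothesised. It does not say when the arm becomes known.

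**Analysis.** The Statistical analyses section commits to intention to treat: "all randomized participants will be included in the analyses regardless of whether they actually completed the intervention or not". The models are regressions and "ANCOVAs with the baseline measure of the concerned outcome as a covariate".

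**The concern.** Randomization protects what is measured before it, and the set of people who are randomized. Here consent, both researcher-guided goals and every T1 score come after it. Three things are then at stake.

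- **The analysis set.** Students can leave between allocation and consent, and they leave no data. The arms differ in burden (three guided VR sessions, a daily app, or goal setting alone). If students know their arm before they decide to attend or consent, the loss can differ by arm.
- **The baseline covariate.** ANCOVA relies on T1 being unaffected by allocation. If knowing the arm changes the answers, the adjustment carries that change into the estimated effect.
- **The goals.** Monthly goal achievement and commitment to the year goal are primary distal outcomes, both scored on goals set at the intake. A researcher who knows the arm could influence how hard or how specific those goals are. Table 2 lists monthly goal achievement at T2 only, so it has no baseline value to adjust for.

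**Working it through.** **1. Order of events.** Setting Recruitment and randomization beside Design gives: portal booking, eligibility and allocation, intake (consent, goals, T1), intervention. This order is stated, not inferred. The order of steps within the intake, and the moment at which the arm is disclosed, are not stated.

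**2. The plan's own figure.** The article gives 199 for 80% power with d = 0.40, alpha 0.05, three conditions and one covariate. With f = d/2 = 0.20, numerator df 1, denominator df = 199 − 3 − 1 = 195 and noncentrality f² × N = 0.04 × 199 = 7.96, power is 80.2%, and 199 is the smallest N that reaches 80%. The figure is reproduced with numerator df 1. It serves here only to scale the loss.

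**3. Loss between allocation and consent.** The article gives no rate, so the share s is an assumption, shown over a range. The Abstract says that 240 will be randomized. If students are lost independently:

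- chance that all 240 attend and consent = (1 − s)^240
- number with consent and T1 = 240 × (1 − s)
- number analysed after the stated 20% drop-out = 240 × (1 − s) × 0.8
- number to randomize to have 240 at intake = 240 / (1 − s), rounded up

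| Assumed s | Chance that nobody is lost | With consent and T1 | After 20% drop-out | Power (df 1) | Randomize for 240 at intake |
|---|---|---|---|---|---|
| 0% | 100% | 240 | 192 | 78.7% | 240 |
| 1% | 9.0% | 238 | 190 | 78.3% | 243 |
| 2% | 0.8% | 235 | 188 | 77.9% | 245 |
| 5% | below 0.001% | 228 | 182 | 76.5% | 253 |
| 10% | below 0.001% | 216 | 173 | 74.4% | 267 |
| 20% | below 0.001% | 192 | 154 | 69.4% | 300 |

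Even a very small loss makes it unlikely that the all-randomized rule can be met in full. The power column applies only if 240 counts students randomized. The Participants and power calculation section speaks of including 240. If that means students enrolled at the intake, the loss costs extra randomizations instead of power, but the conflict with the rule remains.

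**4. Baseline covariate.** If knowing the arm shifts T1 in one arm by δ SD and the outcome's slope on T1 is b, the ANCOVA effect is shifted by −b × δ. The documents give neither quantity. Purely as an illustration, δ = 0.1 and b = 0.5 to 0.6 give 0.05 to 0.06 SD, or 0.05/0.40 = 12.5% to 0.06/0.40 = 15% of the planned d. With δ = 0 there is no bias. The sign depends on the direction of δ, which is unknown.

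**The case against.** A reader might infer three stronger things, and the documents support none of them.

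- **That the all-randomized analysis as a whole cannot be carried out.** It fails only for students who never attend or never consent. The rule as worded is aimed at people who do not complete the intervention, and one can fairly read participants as those who entered the study. On that reading a one-sentence definition closes the gap. What stands is that the text as written says all randomized, and randomization comes first.
- **That T1 and the goals are biased.** Timing alone does not bias a baseline; the arm must be known when T1 is completed or the goals are set. The Blinding section makes this plausible but does not say when disclosure happens. T1 is an online self-report questionnaire, and participants' ignorance of content and hypotheses limits expectancy effects. Goal setting follows the same procedure and published criteria in every arm. The selfie may come after T1, and nothing says that the aged image is shown at the intake. What stands is that participants' ignorance of the hypotheses does not extend to the researcher who guides the goals.
- **That fixed blocks of 9 let staff predict allocations.** This requires staff to see the block boundaries and past allocations. The article does not say who sees the sequence, and such detail normally sits in the full protocol. It is not part of this point.

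The flow chart and the consent material are not visible, so it cannot be fully checked whether some intake step, such as arm-specific consent information, needs the arm earlier.

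**Conclusion.** The point holds in limited form. The stated order puts consent, the month and year goals and every T1 covariate after allocation in an open trial. For any student lost before consent, the stated analysis rule cannot be met. How many that is depends on a rate that the article does not give: about 2 of 240 at an assumed 1%, 12 at 5% and 24 at 10%.

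Differential loss, and influence on T1 or the goals, are risks that depend on the arm being known before these steps are finished. Their size and direction cannot be derived from the documents. This is a worthwhile and inexpensive design improvement, not a demonstration that the results would be biased. It should be made before students are randomized, because no later analysis can restore a baseline that was exposed to knowledge of the arm.

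**What to change.** Within the same intake session, use this order:

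1. consent
2. guided month and year goals
3. T1 questionnaire
4. allocation
5. arm-specific steps: app installation and selfie, or booking of VR sessions

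Define the intention-to-treat set as everyone randomized at step 4. The VR avatar is already made at the first VR session, so the avatar procedures as described do not need the arm before step 4.

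If the present order must stay, conceal the arm from students and intake staff until goals and T1 are complete, define the analysis set as randomized students who consented, and report losses before consent by arm.

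The cost is one reordered session and a short amendment. Staff also cannot prepare for the arm in advance. The change does not protect weekly goals: these are set after allocation by design, with extra researcher guidance in the VR arm.

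### Fixed blocks of 9 in an open trial make about 1 allocation in 7 certain to anyone who knows the block size and the running tally: a modest, avoidable risk

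*Protocol article*

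**What the plan says.** The section Recruitment and randomization fixes one block size and its composition: "using block randomization with blocks of 9, so that within a block three participants are allocated to each of the three conditions". The same sentence sets the time as before the intake and says that "students are assessed for eligibility and randomly assigned to a condition on a 1:1:1 ratio using block randomization with blocks of 9". The section Blinding says the trial is open: "Blinding is not possible as all individuals involved will know whether the app or VR will be used or not".

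Two other statements bear on how far this matters. Students arrange their own appointment: "Students interested in participating can schedule an appointment for the intake using an online portal". The eligibility criteria are short and factual: "We will include first-year students from a university in the Netherlands" and "Students with epilepsy will be excluded due to increased risk of seizures in VR".

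The article does not say who generates or holds the sequence, who knows the block size, or whether those who screen and enrol can see earlier assignments in order.

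**The concern.** With one fixed block size, the balance that the block enforces also gives away information. When an arm's three places in a block are used up, that arm cannot come next. When two arms are used up, the rest of the block is known. In a blinded trial the tally is hidden, so this matters little. In an open trial the arm of each enrolled student is visible to those who deal with that student, and a tally could be kept.

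If a person involved in enrolment could foresee the next arm, even partly, decisions about which student enters next could come to depend on it. The arms differ clearly in burden: three researcher-led VR sessions, daily app use, or goal setting alone. Nearly all outcomes are self-reported. Adjusting for the baseline value of the outcome, as planned, would not fully remove selection on something unmeasured, such as motivation to attend.

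**Working it through.** **Inputs.** Three arms, three places each, block of 9 (Recruitment and randomization). Open trial (Blinding). Target 240 (Participants and power calculation). The article gives no predictability figure to reproduce.

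**Assumption.** The observer knows the block size and every earlier assignment in order. This is the worst case. The article neither states nor excludes it.

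**1. Next arm certain.** The place that is j-th from the end of a block is certain when the last j places all belong to one arm. The probability is 3·C(3,j)/C(9,j).

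- j = 1: 9/9 = 1
- j = 2: 9/36 = 0.250
- j = 3: 3/84 = 0.036

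The sum is 1.286 of 9 places, or 14.3%. Over 26 full blocks: 26 × 1.286 ≈ 33 of 234 allocations.

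**2. At least one arm ruled out.** The last j places must come from at most two arms. The probability is [3·C(6,j) − 3·C(3,j)]/C(9,j).

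- j = 1 and j = 2: 1 each
- j = 3: 57/84 = 0.679
- j = 4: 45/126 = 0.357
- j = 5: 18/126 = 0.143
- j = 6: 3/84 = 0.036

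The sum is 3.214 of 9 places, or 35.7%. This includes the 14.3% from step 1.

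**3. Best guess.** Guessing the arm with most places left is right with probability (largest number of places left)/(places left in the block). An exact recursion over the block gives 4.787 correct of 9, or 53.2%, against 33.3% under simple 1:1:1 randomization.

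**4. Other fixed sizes, same calculation.**

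| Block size | Next arm certain | Best guess right |
|---|---|---|
| 3 | 33.3% | 61.1% |
| 6 | 20.0% | 56.1% |
| 9 | 14.3% | 53.2% |
| 12 | 11.1% | 51.2% |

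**5. Varying sizes in hidden order.** Guessing the arm with the fewest assignments so far needs no knowledge of block sizes, so the best-guess rate of a mixture is the size-weighted mean of the last column.

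- 12 blocks of 9 and 11 of 12 (108 + 132 = 240): (108 × 0.532 + 132 × 0.512)/240 = 52.1%.
- 9 blocks of 6, 10 of 9 and 8 of 12 (54 + 90 + 96 = 240): (54 × 0.561 + 90 × 0.532 + 96 × 0.512)/240 ≈ 53.1%.
- 8 blocks each of 3, 6, 9 and 12 (24 + 48 + 72 + 96 = 240): (24 × 0.611 + 48 × 0.561 + 72 × 0.532 + 96 × 0.512)/240 = 53.8%, slightly worse than fixed blocks of 9.

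For certainty, I simulated 3,000 lists of each of these mixtures. The observer knew which sizes were in use and all past assignments, but not the order of the blocks.

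| Mixture | Next arm certain | At least one arm ruled out |
|---|---|---|
| 9 and 12 | 3.8% | 10.6% |
| 6, 9 and 12 | 2.3% | 6.5% |
| 3, 6, 9 and 12 | 2.2% | 6.2% |

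The same program with fixed blocks of 9 returned 14.3% and 35.7%, which agrees with steps 1 and 2.

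**The case against.** The strongest reply is that the route from predictability to bias is narrow. Foreseeing an arm requires the tally in allocation order. The Blinding section concerns knowledge of the treatment delivered, not access to the sequence. A condensed article commonly leaves custody of the list to the full protocol, so its silence there is not a fault. Even the fully informed observer is certain only about once in seven, and the 36% figure merely excludes one or more of three arms. Varying block sizes also leave the best-guess rate close to 53%. All of this stands, and it sets the size of the point. It does not remove the point, because a single fixed block size in an open trial is a stated choice, and most of the certainty that it creates can be avoided.

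A reader might infer three stronger things that the text does not support.

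- **Staff choose whom to book and when.** Students book through a portal, and the stated criteria (first-year student, no epilepsy) leave little room for judgement.
- **Eligibility and allocation are one act.** The sentence names eligibility first and assignment second. It does not say that they coincide or that one person does both.
- **240 not being a multiple of 9 is a defect.** The article says "we aim to include 240 participants, i.e., 80 participants per condition", which is a target. Since 240 = 26 × 9 + 6, stopping at exactly 240 leaves each arm with 78 to 81 students. Pairwise power at d = 0.40, before drop-out and without a covariate, is 71.6% at 80 v 80 and 71.3% at 78 v 81. The difference is negligible.

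**Conclusion.** The concern holds as a modest and avoidable design risk. Under the stated scheme, an observer who knows the block size and the running tally is certain of the next arm for 14% of allocations, can rule out at least one arm for 36%, and guesses correctly 53% of the time instead of 33%. These figures are upper bounds on what staff could know, since they assume full sight of past assignments in order. Anyone without that sight knows less.

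The documents give no basis for estimating a bias in any outcome, and none is claimed. Self-booking and factual criteria limit what could be done with the information. The case for change is that the remedy costs very little.

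**What to change.** In Recruitment and randomization, replace the fixed blocks of 9 with blocks of varying sizes in random order that sum to 240. Two lists that work are 12 blocks of 9 with 11 of 12, and 9 blocks of 6 with 10 of 9 and 8 of 12. Avoid blocks of 3, which are the most predictable and would push the best-guess rate above its present value. State that sizes and order are withheld from staff who screen and enrol, and keep the sizes out of any text those staff use while recruitment is open. State also that each assignment is released only after the eligibility decision has been recorded, which makes the order already implied by the text explicit.

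The cost is regenerating the list and setting the release order, with no extra participants or staff. If recruitment is under way, the change can apply to the remaining allocations. If it is complete, report who held the sequence, who knew the block size, and how many allocated students did not complete the intake, by arm.
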